**Methods:**

This longitudinal observational study will recruit kidney transplant recipients aged ≤18 years who have received a parental donor kidney transplant across 4 countries (Australia, New Zealand, United Kingdom and the Netherlands) between 1990 and 2020. High resolution human leukocyte antigen (HLA) typing of both recipients and corresponding parental donors will be undertaken, to provide an in-depth assessment of immunological compatibility. The primary outcome is a composite of de novo donor-specific anti-HLA antibody (DSA), biopsy-proven acute rejection or allograft loss up to 60-months post-transplantation. Secondary outcomes are de novo DSA, biopsy-proven acute rejection, acute or chronic antibody mediated rejection or Chronic Allograft Damage Index (CADI) score of > 1 on allograft biopsy post-transplant, allograft function, proteinuria and allograft loss. Using principal component analysis and Cox proportional hazards regression modelling, we will determine the associations between defined sets of immunological and clinical parameters that may identify risk stratification for the primary and secondary outcome measures among young people accepting a parental donor kidney for transplantation. This study design will allow us to specifically investigate the relative importance of accepting a maternal compared to paternal donor, for families deciding on the best option for donation.

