### Outcome measures

The primary outcome is the composite of de novo DSA (defined as mean fluorescence intensity [MFI] of over 500), or any biopsy-proven acute rejection or allograft loss (defined as returning to dialysis or death with functioning allograft) after parental donor kidney transplantation up to 60-months post-transplant. Secondary outcomes are individual components of the primary composite outcome (development of de novo DSA, any biopsy-proven acute rejection, allograft loss at 60-months post-transplant but also extended follow-up to 120-months post-transplant), acute or chronic AMR (including the presence of TG) or Chronic Allograft Damage Index (CADI) score of > 1 on allograft biopsy post-transplant, allograft function (creatinine-derived estimated glomerular filtration rate [eGFR] using the Chronic Kidney Disease-Epidemiology Collaboration [CKD-EPI] equation for recipients aged ≥16 years [32] or bedside Schwartz equation for recipients aged < 16 years [33–35]), and urine proteinuria.

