#### Assessment for acute rejection and CADI

Episodes of biopsy-proven acute and chronic rejection (diagnosed on protocol or clinical indication biopsies) post-transplant will be assessed and reported according to the validated Banff classification [38]. Consistent with this, each rejection episode will be categorized as acute, chronic or acute on chronic; and further stratified to cellular, vascular, antibody mediated or mixed pattern rejections. The most severe type of rejection in those with a mixed pattern will be considered the dominant lesion (i.e. vascular or antibody-mediated > cellular rejections). TG (Banff cg 1-3) will be coded according to the Banff classification and is considered a morphological manifestation of chronic AMR [39].

The CADI score quantifies the amount of chronic damage to the allograft, with the score calculated from a total of six parameters of: (a) diffuse or focal inflammation and (b) fibrosis in the interstitium, (c) mesangial matrix increase and (d) sclerosis in glomeruli, (e) intimal proliferation of vessels, and (f) tubular atrophy; with each individual parameter being scored between 0 and 3 as described in other studies [40]. The CADI score is a global standardized scoring system based on pre-defined criteria and is considered part of standard reporting in all pathology laboratories. Previous studies have consistently shown that an elevated CADI score correlates with acute rejection as well as chronic rejection and allograft loss up to 4 years post-transplant, indicating that CADI score has important prognostic significance [41–45].

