Renal allograft biopsies (protocol or clinical indication biopsies) are frequently undertaken after kidney transplantation and are typically prepared into formalin-fixed paraffin-embedded tissue blocks or stored as frozen tissues. Representative images or whole slide imaging (using digital microscopy or site-specific systems such as the Sysmex system according to site availability) for histological scoring to capture the abnormal findings will be requested from each histopathology department, which will comprise of at least one Periodic acid–Schiff (PAS) and one Trichrome-stained images (where possible). If multiple biopsy specimens were available in the first 12 months post-transplant, only tissues from two of these biopsies (one between 0 and 6 months and the other between > 6-12 months if available) will be imaged. A nominated blinded pathologist will re-score the stored digital images (where available) in accordance with the established CADI parameters and Banff criteria for rejection and chronicity [41, 46].

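### The histological secondary outcome joins antibody-mediated rejection to CADI > 1 by 'or', so it is not specific to antibody-mediated or chronic damage and can dilute an effect on AMR

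*Protocol article*

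**What the plan says.** The Outcome measures section gives, within its list of secondary outcomes, "acute or chronic AMR (including the presence of TG) or Chronic Allograft Damage Index (CADI) score of > 1 on allograft biopsy post-transplant". The abstract repeats the item: "acute or chronic antibody mediated rejection or Chronic Allograft Damage Index (CADI) score of > 1 on allograft biopsy post-transplant". Neither place ties it to a time point, although the Outcome measures sentence gives 60 and 120 months for the components of the primary composite.

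The section Assessment for acute rejection and CADI describes the score. Its parameters include "diffuse or focal inflammation and (b) fibrosis in the interstitium, (c) mesangial matrix increase and (d) sclerosis in glomeruli", followed by intimal proliferation and tubular atrophy, "with each individual parameter being scored between 0 and 3". The section states the purpose: "The CADI score quantifies the amount of chronic damage to the allograft". It also reports that "an elevated CADI score correlates with acute rejection as well as chronic rejection and allograft loss up to 4 years post-transplant". It gives no reason for a cut at > 1.

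The same section counts rejection found on protocol and on indication biopsies. Where several biopsies exist in the first year, two are imaged: "one between 0 and 6 months and the other between > 6-12 months if available". Each rejection episode is typed as cellular, vascular, antibody mediated or mixed, and transplant glomerulopathy (TG) is coded by its own Banff grade. The Statistical analysis section plans a separate model for each secondary outcome.

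**The concern.** The item is the only listed outcome that names AMR, TG or CADI. The eplet, amino acid, electrostatic and T-cell-help scores are aimed largely at antibody responses, so this is where a reader would look for a link between compatibility, or donor parent, and antibody-mediated or chronic injury.

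An 'or' between a specific diagnosis and a low cut on a broad damage score lets the second part supply events that have nothing to do with the first. Three sources follow from the protocol's own definitions:

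- interstitial inflammation in a cellular rejection, already counted under biopsy-proven acute rejection;
- mild fibrosis, sclerosis or intimal change that was in the parent's kidney at transplant, since no baseline biopsy or change from baseline is described;
- minor non-specific scarring.

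If the item is modelled as written, a true association with AMR could be weakened or missed, and an association that is found could not be assigned to AMR or to chronic damage.

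**Working it through.** The documents give no figure for this outcome, so there is nothing to reproduce. The check has three parts.

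**1. What the cut admits.** Inputs: six parameters, each graded 0-3 (Assessment for acute rejection and CADI); event if CADI > 1 (Outcome measures).

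- Maximum score: 6 × 3 = 18. The lowest qualifying total is 2.
- Possible score patterns: 4^6 = 4096. Those that do not qualify are all zeros (1) and a single grade-1 lesion (6), 7 in all. The other 4096 − 7 = 4089 qualify. This counts patterns, not patients.
- Inflammation grade 2, all else 0: total 2, an event with no antibody-mediated and no chronic lesion.
- Fibrosis grade 1 plus tubular atrophy grade 1: total 2, an event.
- Inflammation grade 1, all else 0: total 1, not an event.

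**2. How often that might happen.** The documents give no lesion frequencies, so these are assumptions. Let each of the six lesions be present at grade 1 with probability q, independently, and otherwise absent. Then P(CADI > 1) = 1 − (1 − q)^6 − 6q(1 − q)^5, and for two independent biopsies the chance of at least one event is 1 − (1 − P)^2.

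| q | one biopsy | at least one of two |
|---|---|---|
| 0.1 | 11% | 22% |
| 0.2 | 34% | 57% |
| 0.3 | 58% | 82% |

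The range is wide. Lesions in one kidney, and repeat biopsies of it, are unlikely to be independent. Positive correlation between biopsies would lower the last column.

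**3. What dilution could do.** Assumed, not in the documents: AMR or TG in 15% v 8%; the 520 expected pairs split equally, 260 per group, all evaluable; a CADI-only event with probability b among the remaining recipients, the same in both groups. The combined rate is a + (1 − a)b, where a is the AMR or TG rate. Power is for a two-sided 5% test of two proportions, a simplification of the planned models.

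| b | combined rates | difference | ratio | power |
|---|---|---|---|---|
| 0 | 15.0% v 8.0% | 7.0 points | 1.88 | 71% |
| 0.2 | 32.0% v 26.4% | 5.6 points | 1.21 | 29% |
| 0.4 | 49.0% v 44.8% | 4.2 points | 1.09 | 16% |
| 0.6 | 66.0% v 63.2% | 2.8 points | 1.04 | 10% |

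For example, at b = 0.2: 0.15 + 0.85 × 0.2 = 0.32 and 0.08 + 0.92 × 0.2 = 0.264.

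**The case against.** **The 'or' may separate two outcomes.** It sits inside a long list, and the figure that shows the outcome measures is not available. That possibility stands. Commas divide the other items, however, and the same section uses 'or' to build the primary composite, so one combined item is the natural reading. If two outcomes are meant, the dilution of AMR disappears, but CADI > 1 can still be met by inflammation alone or by donor-derived lesions.

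**The components are recorded apart.** This stands. Rejection type and TG are coded separately, a blinded pathologist re-scores CADI and the Banff criteria where images exist, and any biopsy-proven acute rejection is its own secondary outcome, which includes acute antibody-mediated episodes. A reader might infer that the study cannot measure antibody-mediated or chronic damage. The documents do not support that: every AMR or TG case is captured, and five of the six CADI parameters are structural. The fault is low specificity of the outcome as worded.

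**Cellular rejection does not always qualify.** Correct. It needs inflammation of grade 2 or more, or a second lesion.

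**The event rate is not known to be high.** Correct. A reader might infer from the low cut that most recipients with repeat biopsies become events, or that the outcome is near its ceiling. Both rest on assumed lesion rates and independence; at q = 0.1 only 11% of single biopsies qualify.

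**Donor quality is partly handled.** Donor age and comorbidity are collected, and donor age is named for additional models. Adjustment helps, but it does not change what counts as an event.

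**The cut and the time windows may be justified elsewhere.** They may be, in the full protocol or in the cited studies. The point therefore rests on the wording and scoring that the article does state, not on a missing rationale. Overlap with the acute rejection outcome is likewise no error in itself.

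**Conclusion.** The concern holds in limited form. Under the natural reading, the outcome counts as an event AMR, TG or any CADI total of 2 or more, and that total can be reached by grade 2 inflammation alone or by two grade-1 lesions, some possibly donor-derived. This follows from the protocol's own scoring and needs no assumption. The combined item is therefore not specific to antibody-mediated or chronic damage and can dilute an effect on AMR.

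How much it dilutes is unknown. The fall in power from about 71% to between 29% and 10% depends on assumed AMR rates, on assumed CADI-only rates of 20% to 60%, and on those events being unrelated to donor parent. It shows what could happen and is no estimate for this cohort. The primary outcome and its sample size are not affected.

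**What to change.** - List AMR (acute or chronic, including TG) and CADI as two secondary outcomes, each with its own model.
- Analyse CADI as the 0-18 score rather than only as > 1, accounting for time from transplant to biopsy and for donor age.
- Repeat the CADI analysis without the inflammation parameter as a sensitivity analysis.
- Do not adjust for the 0-6 month score in the main analysis. It is measured after transplant and may already reflect incompatibility, so adjusting could remove part of the effect under study. For a related reason, do not confine the main CADI analysis to biopsies at > 6-12 months, which would discard later chronic damage.

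The data are already to be collected, so the cost is a change of wording and one extra model. The downsides are fewer events for AMR and TG alone, and a CADI analysis limited to recipients who had a biopsy.

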#### De novo DSA

Post-transplant sera of all recipients are tested pre-transplant, when clinically indicated or routinely at pre-specified time-points post-transplant (in some centres) for de novo DSA directed against either the maternal or paternal donor HLA across HLA-A, −B, −C, −DRB1, −DRB3/4/5, −DPA1, −DPB1, −DQA1 and -DQB1 alleles. In brief, an aliquot of a single antigen bead (SAB) mixture will be incubated with a small volume of patients’ sera (approximately 50 μl) containing the anti-HLA antibody as per manufacturer’s instructions. The analysis will be undertaken on a Luminex (or equivalent) platform and the reactivity will be determined with the manufacturer’s software and expressed as mean fluorescence intensity (MFI) for each mismatched HLA. Antibodies to these HLA alleles with MFI of varying thresholds (from MFI ≥ 500) will be considered a “positive result” because we and others have shown a consistent association between the presence of pre-transplant DSA with MFI ≥500 and a heightened risk of rejection after kidney transplantation [36, 37]. The MFI threshold value of ≥500 is defined using the Luminex platform. The time-points for the monitoring and testing for pre-transplant and de novo DSA will be undertaken according to the standard policies of each participating site; typically, pre-transplant, annually post-transplant and/or when clinically indicated (during episodes of allograft dysfunction or acute rejection).

#### Assessment for acute rejection and CADI

Episodes of biopsy-proven acute and chronic rejection (diagnosed on protocol or clinical indication biopsies) post-transplant will be assessed and reported according to the validated Banff classification [38]. Consistent with this, each rejection episode will be categorized as acute, chronic or acute on chronic; and further stratified to cellular, vascular, antibody mediated or mixed pattern rejections. The most severe type of rejection in those with a mixed pattern will be considered the dominant lesion (i.e. vascular or antibody-mediated > cellular rejections). TG (Banff cg 1-3) will be coded according to the Banff classification and is considered a morphological manifestation of chronic AMR [39].

The CADI score quantifies the amount of chronic damage to the allograft, with the score calculated from a total of six parameters of: (a) diffuse or focal inflammation and (b) fibrosis in the interstitium, (c) mesangial matrix increase and (d) sclerosis in glomeruli, (e) intimal proliferation of vessels, and (f) tubular atrophy; with each individual parameter being scored between 0 and 3 as described in other studies [40]. The CADI score is a global standardized scoring system based on pre-defined criteria and is considered part of standard reporting in all pathology laboratories. Previous studies have consistently shown that an elevated CADI score correlates with acute rejection as well as chronic rejection and allograft loss up to 4 years post-transplant, indicating that CADI score has important prognostic significance [41–45].

Renal allograft biopsies (protocol or clinical indication biopsies) are frequently undertaken after kidney transplantation and are typically prepared into formalin-fixed paraffin-embedded tissue blocks or stored as frozen tissues. Representative images or whole slide imaging (using digital microscopy or site-specific systems such as the Sysmex system according to site availability) for histological scoring to capture the abnormal findings will be requested from each histopathology department, which will comprise of at least one Periodic acid–Schiff (PAS) and one Trichrome-stained images (where possible). If multiple biopsy specimens were available in the first 12 months post-transplant, only tissues from two of these biopsies (one between 0 and 6 months and the other between > 6-12 months if available) will be imaged. A nominated blinded pathologist will re-score the stored digital images (where available) in accordance with the established CADI parameters and Banff criteria for rejection and chronicity [41, 46].

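### CADI may be re-scored from whole slides or from images requested to show abnormality; the instruction conflicts with itself and may inflate the CADI > 1 outcome by an amount that may differ by site

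*Protocol article*

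**What the plan says.** All quotes are from the Protocol article, Assessment for acute rejection and CADI.

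- **Image source.** Two kinds are allowed: "Representative images or whole slide imaging (using digital microscopy or site-specific systems such as the Sysmex system according to site availability").
- **Purpose and supplier.** These images "for histological scoring to capture the abnormal findings will be requested from each histopathology department".
- **Minimum set.** The request is for "at least one Periodic acid–Schiff (PAS) and one Trichrome-stained images (where possible"). The text gives no rule for choosing fields and none for making the two image types comparable.
- **Reader.** "A nominated blinded pathologist will re-score the stored digital images (where available) in accordance with the established CADI parameters" and the Banff criteria.
- **What is scored.** "The CADI score quantifies the amount of chronic damage to the allograft", from six parameters, "with each individual parameter being scored between 0 and 3 as described in other studies".

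Under Outcome measures, a CADI score of > 1 is a secondary outcome, listed together with acute or chronic antibody-mediated rejection. It is not part of the primary composite.

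**The concern.** A score for how much of the tissue is damaged needs the undamaged tissue in view as its denominator. A whole slide provides that. A few fields sent because they show the lesion do not. The plan feeds both kinds of material into one score and gives, as the purpose of the images, a reason that favours the abnormal field.

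The central pathologist's blinding protects against knowledge of donor parent or clinical course at the reading. It cannot undo a choice of field made before the images arrived.

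At stake is the CADI > 1 outcome: its overall rate, and comparisons across sites that supply different kinds of image. The Statistical analysis section builds separate models for each secondary outcome, so an artefact of image supply would enter the CADI model as if it were biology.

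**Working it through.** The document gives no CADI prevalence, field count, grading thresholds or image type by site, so there is no planned figure to reproduce. The check has three parts.

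**1. How low the cut-off is.** Six parameters scored 0 to 3 give a maximum of 6 × 3 = 18. Scores are whole numbers, so > 1 means 2 or more. One parameter graded 2, or two parameters graded 1, is enough.

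**2. What selection does to one parameter.** *Assumed* (not in the document): 12 equal fields per biopsy, and grades 0/1/2/3 for extent < 5%, 5–25%, 25–50% and > 50%. Let a lesion lie in one field only and cover a share *x* of it.

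- Whole-slide extent is *x*/12. It reaches grade 1 only if *x* ≥ 12 × 5% = 60%.
- In the lesion field alone, the extent is *x*: grade 2 from 25%, grade 3 above 50%.
- So for any *x* from 25% up to 60%, this parameter scores 0 on the whole slide and 2 or 3 on the selected field. That alone takes the biopsy from CADI 0 to CADI > 1.

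**3. Direction over all six parameters.** Two simulations, 40,000 biopsies per scenario, both with worst-case selection.

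*Model A:* 12 fields and the grades above. Extent per parameter is beta-distributed between biopsies and between fields, with field concentration 5. The field with the largest total abnormality is the one scored. The ranges come from two runs, one of them with between-biopsy concentration 5.

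*Model B:* 20 fields, each affected or not. Grades 0/1/2/3 for an affected share ≤ 10%, ≤ 25%, ≤ 50% and > 50%. The three most abnormal fields are scored.

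| Model | Mean extent or share | CADI > 1, whole slide | CADI > 1, selected |
|---|---|---|---|
| A | 2% | 19% | 55–56% |
| A | 3% | 31–33% | 70–73% |
| A | 5% | 55–58% | 87–90% |
| B | 3% | 4% | 94% |
| B | 5% | 20% | 99% |
| B | 10% | 68% | > 99% |

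The shift is upward in every row. In Model A, varying the between-biopsy concentration over 5–20 and the field concentration over 2, 5 and 20 moves the gap between about 22 and 58 percentage points. At a nominal 3%, Model A gives a gap of about 39–40 points and Model B about 94 − 4 = 90. The size therefore comes from the assumptions.

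The number of fields matters as well. In Model A, one *unselected* field scores close to or below the whole slide. In Model B, three unselected fields give 41%, 59% and 82% against 4%, 20% and 68%, because one affected field in three already counts as 33%. Whole slides and small field sets need not be interchangeable even without selection.

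**The case against.** **The sentence says representative.** That is the only word describing how images are chosen, and it points away from picking the worst field. The phrase about abnormal findings also covers whole slides, where nothing is selected, so it can be read as the purpose of scoring. This stands in part: inflation is a risk and not an established result. But a department that receives both instructions can reasonably send the lesion, so the wording needs correcting.

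**No site is documented as using either mode.** This is correct. The availability clause concerns equipment, and local choice of fields is inferred from the request going to each department. The text nevertheless permits a mixture across 5 + 1 + 13 + 3 = 22 centres.

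**The article condenses a fuller protocol.** The absence of a field count or magnification is therefore no finding. The objection does not reach the point made here, which is the purpose the article does state and the two unequal inputs it does allow.

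**Stronger readings the document does not support.**

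- A reader might infer that CADI *is* inflated, by a known amount at each site. The figures above assume the worst field is sent and do not estimate the bias in this study.
- A reader might infer that the artefact would look like failed validation between the Australia/New Zealand and the UK/Netherlands cohorts. The Statistical analysis section derives and validates archetypes that use time to the primary composite, which excludes CADI, and then models the combined cohorts.
- A reader might infer bias between maternal and paternal donors. That would need image type to be related to donor parent, and nothing in the document says so.

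**Conclusion.** The point holds as a conflict in a stated procedure. Scoring may use whole slides or locally supplied images, and the request asks for images that are both representative and meant to show abnormality. Fields supplied for their abnormality overstate a score of the amount of damage, and a cut-off reached at 2 of 18 points is sensitive to that. The CADI > 1 outcome may be inflated, to a degree that may differ by site. Central blinding does not remove this.

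The direction rests on CADI being graded by extent, which is inferred from its description as an amount because the 0–3 thresholds are not given. The size is unknown. The outcome is secondary and the primary composite is untouched, so this is worth correcting before images are collected but does not threaten the main result.

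**What to change.** In Assessment for acute rejection and CADI:

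1. Delete capturing abnormal findings as the basis for the image request.
2. Ask for whole-slide imaging wherever the site has it. Elsewhere, ask for fields taken by a fixed rule that does not depend on abnormality, with the number of fields per stain stated.
3. Record the image type for each biopsy as it is collected, since it may be hard to reconstruct later.
4. Stratify the CADI > 1 analysis by image type, or adjust for it, and add a sensitivity analysis limited to whole-slide biopsies.

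Keep the central blinded re-scoring. The section describes CADI as "considered part of standard reporting in all pathology laboratories", which makes local reports a tempting substitute where images are poor. Using them would give up blinding and the single reader, so they should not replace the central score.

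The cost is a wording change, slightly more imaging work at sites without a scanner, and a smaller sample in the sensitivity analysis. No extra biopsy or reader is needed.
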